## Abstract

**Background:**

Ambient air pollution, detrimental built and social environments, social isolation (SI), low socioeconomic status (SES), and rural (versus urban) residence have been associated with cognitive decline and risk of Alzheimer’s disease and related dementias (ADRD). Research is needed to investigate the influence of ambient air pollution and built and social environments on SI and cognitive decline among rural, disadvantaged, ethnic minority communities. To address this gap, this cohort study will recruit an ethnoracially diverse, rural Florida sample in geographic proximity to seasonal agricultural burning. We will (1) examine contributions of smoke-related fine particulate matter (PM_2.5_) exposures to SI and cognitive function; (2) determine effects of built and social environments on SI and cognitive function; and (3) contextualize SI and cognitive function among residents from different ethnoracial groups during burn and non-burn seasons.

**Methods:**

We will recruit 1,087 community-dwelling, dementia-free, ≥45-year-olds from five communities in Florida’s Lake Okeechobee region. Over 36 months, participants will complete baseline visits to collect demographics, health history, and health measurements (e.g., blood pressure, body mass index) and 6-month follow-ups assessing cognitive function and social isolation at each visit. A subsample of 120 participants representative of each community will wear smartwatches to collect sensor data (e.g., heart rate) and daily routine and predefined activities (e.g., GPS-captured travel, frequent destinations) over two months. Ecological momentary assessments (EMA) (e.g., whether smoke has bothered participant in last 30 minutes) will occur over two months during agricultural burning and non-burning months. PurpleAir monitors (36 total) will be installed in each community to continuously monitor outdoor PM_2.5_ levels.

**Discussion:**

We expect to identify individual- and community-level factors that increase the risk for SI and cognitive decline in a vulnerable rural population.

## Introduction

Alzheimer’s disease and related dementias (ADRD) comprise multiple neurodegenerative diseases with differing neuropathological origins, including Alzheimer’s disease, Lewy body disease, and frontotemporal degeneration [1–3]. Over time, the neuropathological burden of these diseases leads to dementia, which is the “loss of memory, language, problem-solving and other thinking abilities that are severe enough to interfere with daily life” [4]. ADRD risk increases with age and is 1.5 to 2 times higher among Black and Hispanic individuals, who are more likely to have lower educational attainment and chronic conditions (e.g., diabetes, hypertension, cardiovascular disease) that are known risk factors for ADRD [5, 6]. Social determinants of health (SDOH), which are the conditions where people live, work, worship, play, and age, have been increasingly implicated in increasing ADRD risk, particularly for minoritized and socioeconomically disadvantaged communities [7–9]. For instance, Black and Hispanic older adults tend to live in neighborhoods with greater area deprivation and lower greenspace access, and these factors have been associated with greater risk of cognitive decline and dementia in numerous studies [10–14].

In addition, both air pollution and social isolation are key SDOH that have been named by the Lancet Commission as ADRD risk factors [6, 15], and exposures to ambient air pollution and social isolation are more prevalent in historically disadvantaged communities [16, 17]. Ambient air pollution, including particulate matter of <2.5μm in size (PM_2.5_), has been shown to increase morbidity and mortality and ADRD risk, particularly among urban-dwelling Hispanic and Black individuals [18–23]. The preponderance of air quality health effects studies in the U.S. have been conducted using U.S. Environmental Protection (EPA) Agency Air Quality System data and have focused largely in urban areas where monitors are located. Agricultural burns, like wildfire smoke, have smoke plumes with large spatiotemporal gradients which frequently impact sparsely populated areas with limited extant monitoring. Yet, agricultural fires, unlike wildfires, have constrained size, intensity, and smoke production, thereby testing the limits of detection by satellite. A major advantage of studying agricultural burns is that in contrast to wildfires, agricultural fires follow a predictable schedule in circumscribed spatial areas, enabling ground monitoring. However, studies on the health effects from rural agricultural fires which disproportionately impact Black and Hispanic communities are limited [23].

Social isolation, recognized as a significant threat to public health by the U.S. Surgeon General, is characterized by the lack of social engagement, supportive social networks, and/or participation in social activities [24]. Numerous studies have linked social isolation to poorer cognitive function and ADRD risk [25–31]. For example, 70-year olds from the Lothian Birth Cohort who lived alone had slower processing speed and those who reported greater loneliness had worse overall cognitive function [27].

While sufficient evidence is available to implicate social isolation in increasing ADRD risk, the published studies are primarily limited to urban and White populations, with little known about how these factors impact rural and ethnoracially diverse populations that are most vulnerable to developing ADRD.

Neighborhood social and built environments are SDOH that have also been associated with cognitive function and ADRD risk [8, 10, 11, 32, 33]. For instance, neighborhood social environments, such as living in areas with greater area deprivation, greater psychosocial disorder (e.g., crime), and ethnoracial segregation, have been associated with worse ADRD-related outcomes in prior studies [13, 34, 35]. Built environments are manmade physical environments including but not limited to transportation and pedestrian networks, social and walking destinations (shops, libraries, banks, restaurants), parks and other greenspaces, and health care facility access. A systematic review of studies on various built environment factors found the strongest evidence to date was for associations between greater walking/social destinations and more greenspace in the neighborhood and better cognitive function and lower dementia risk [32]. However, similar to the studies focused on either social isolation or air pollution exposure and ADRD risk, few studies of neighborhood environments and ADRD have centered on rural, ethnoracially diverse older adults.

Rural residence (versus urban) has been associated with higher incidence or prevalence of ADRD [36, 37]. Some reasons for this may be lower educational attainment and lower access to health care and other resources that help maintain brain health into later life [38–40] However, the relationship between rural/urban residence and ADRD risk is not straightforward given the differences in access to care and diagnostic services in rural areas that may lead to underdiagnosis of ADRD, in addition to the significant differences in the ethnoracial groups living in rural areas depending on U.S. region [41]. Overall, few studies have been conducted on risk factors for ADRD among ethnoracially diverse rural populations in the U.S.

Altogether, the extant literature suggests that several SDOH at the environmental (i.e., air pollution, neighborhood social and built environments, rural residence) and individual level (i.e., ethnoracial group and social isolation) increase ADRD risk. However, no known studies have investigated how all these factors considered together contribute to cognitive decline in older adults, particularly those living in rural areas with varying seasonal levels of PM_2.5_ due to agricultural burning. To address this significant scientific gap, the Rural Roads to cognitive Resilience (RRR) cohort study will recruit a sample of ethnoracially diverse (predominantly Black and Hispanic), socioeconomically disadvantaged older adults living in a rural agricultural area surrounding Lake Okeechobee in South Central Florida. The study, which targets a region beset by a combination of the aforementioned and other unique ADRD risks, aims to (1) examine the contribution of agricultural smoke-related PM_2.5_ exposures to social isolation and cognitive function, (2) determine the effects of the built (e.g., park space) and social environment (e.g., neighborhood disadvantage) on social isolation and cognitive function, and (3) contextualize social isolation and cognitive function among residents from different ethnoracial groups using ecological momentary assessment (EMA) and smartwatch sensor-derived behavior models with a subsample of 120 stratified by Lake O communities during agricultural burn and non-burn seasons.

## Materials and methods

### Setting and design

#### Study summary

Rural Roads to cognitive Resilience (RRR) is a longitudinal, observational cohort study that will broadly collect data on ambient air pollution exposure, neighborhood built and social environments, social isolation, and cognitive functioning among participants 45 and older living in rural communities surrounding Lake Okeechobee, Florida. The study is comprised of two data collection efforts: (i) a 36-month study of ~1,000 individuals to investigate social isolation and cognitive function may be affected by ambient PM_2.5_ and neighborhood built/social environments, and (ii) a smartwatch study subsample of ~120 participants recruited from the 36-month study.

#### Setting

The Everglades Agricultural Area in South Central Florida is the largest sugarcane-producing region in the U.S. from ~October to May each year, sugar companies employ farmworkers to prepare 400,000 acres of fields for harvesting by burning the sugarcane outer leaves. The population surrounding Lake Okeechobee (Lake O) demonstrates a multitude of disparities that are risk factors for ADRD. For example, in the town of Belle Glade, 40% of the population did not graduate from high school, health literacy is equivalent to 7th grade, 91% are minoritized ethnic groups, the area has limited healthcare access, and poverty affects 41% of the population [42]. In addition, during burns, residents surrounding Lake Okeechobee describe experiences of stench, eye irritation, feeling tight in the chest, and outdoor areas covered in soot, preventing outdoor social engagement [43]. Typically, the background PM_2.5_ levels in the Lake O region are relatively low, but increases of up to 2μg/m^3^ occur during agricultural burning season [44]. Altogether, Lake O provides a fitting setting to study the impact of air pollution on diverse, rural, and high-risk communities.

#### Specific aims

Aim 1. Examine the contribution of particulate matter <2.5μm (PM_2.5_) exposures to social isolation and cognitive function (CF), through multilevel growth modeling.

Aim 1a. Examine baseline levels and growth trajectories of SI and CF associated with changes in PM_2.5_ during agricultural burn and non-burn seasons over a 36-month period, accounting for individual- and neighborhood- level characteristics.Aim 1b. Examine the effect modification of race/ethnicity on the relationship of PM_2.5_ on baseline levels and growth trajectories of SI and CF, accounting for individual- and neighborhood-level characteristics.

Aim 2. Determine the effects of the built environment (e.g., retail destinations, park space) and social environment (e.g., crime, SES) on SI and CF through linear mixed modeling.

Aim 2a. Examine SI and CF associated with the built and social environment over a 36-month period (baseline, and FY 1,2,3), controlling for individual- and other neighborhood-level characteristics.Aim 2b. Explore the effect modification of race/ethnicity on the relationship of the built and social environment with SI and CF, in view of their educational and social disadvantage.

Aim 3. Contextualize SI and CF among residents from different ethnoracial groups using EMA and sensor- derived behavior models during burn and non-burn seasons in a subsample of 120 ethnoracially diverse participants, stratified by Lake O communities.

Aim 3a. Examine residents’ momentary changes in behavioral markers, mood, and cognitive performance, associated with changes in air quality and the social and built environment.Aim 3b. Characterize differences among ethnoracial groups and between women and men in their momentary changes in behavioral markers, mood, and CF performance in response to changes in air quality and the social and built environment.

#### Enrollment

RRR will recruit a sample of approximately 1,000 individuals located in Hendry, Glades, Okeechobee, and Palm Beach counties. More specifically, participants will be enrolled from 4 rural communities (i.e., Clewiston, Pahokee/Canal Point, Okeechobee, Belle Glade/South Bay) and 1 suburban/urban community (i.e., Royal Palm Beach). The communities were chosen to provide diversity in ethnoracial and socioeconomic groups and socioeconomic status (higher Area Deprivation Index score: more deprived neighborhood) and sufficient variation in social and built environments at the census block group level to successfully complete the study aims (Figs 1–4).

**Fig 1 pone.0312660.g001:**
[figure not shown]
Florida communities included in the study. * Exact locations/census block groups included will depend on recruitment. Map image is the intellectual property of Esri and is used herein under license. Copyright © 2020 Esri and its licensors. All rights reserved.

**Fig 2 pone.0312660.g002:**
[figure not shown]
Variation in neighborhood percentage of Hispanic residents by community. * Exact locations/census block groups included will depend on recruitment. Map image is the intellectual property of Esri and is used herein under license. Copyright © 2020 Esri and its licensors. All rights reserved.

**Fig 3 pone.0312660.g003:**
[figure not shown]
Variation in neighborhood percentage of Black/African American residents by community. * Exact locations/census block groups included will depend on recruitment. Map image is the intellectual property of Esri and is used herein under license. Copyright © 2020 Esri and its licensors. All rights reserved.

**Fig 4 pone.0312660.g004:**
[figure not shown]
Variation in Area Deprivation Index (neighborhood socioeconomic status) by community. * Exact locations/census block groups included will depend on recruitment. Map image is the intellectual property of Esri and is used herein under license. Copyright © 2020 Esri and its licensors. All rights reserved.

#### Screening and inclusion and exclusion criteria

Eligible participants will be:

Community-dwelling individuals from the Lake Okeechobee region in Florida,Age 45 years and older,English, Spanish, or Creole speakers,Able to participate in study activities,Staying in the area for at least 12 months, and,Not leaving for an extended period during the summer months.

In addition to these criteria, the street address and years lived at that location will be determined. Potential participants will also be asked their date of birth (from which age is auto-calculated), their primary language, and years of education. As a means of subjective cognitive functional assessment, everyone who participates in the pre-screening will also be asked “Do you feel that your memory is getting worse?” In addition, the inclusion form will collect the town and site where the data collection will occur. Potential participants will then be pre-screened for dementia and excluded if MoCA-5 minute (Mini MoCA) scores are <12 (clinically important risk of cognitive impairment) [45]. This brief task takes ≤5 minutes and assesses the domains of attention, executive function/language, orientation, and memory. If they are unable to obtain the minimum score of 12 (adjusted for years of education), they will be referred to their provider (if unavailable, a local provider who has agreed to follow up with an assessment) and provided with a small appreciation gift for their time (writing pen) and a flyer regarding resources on brain health.

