#### Timeline of study assessments

For the 36-month study, at the baseline visit (T0), which occurs immediately after consent, individuals will provide data on sociodemographics, health history, and health behaviors. Participants will return to complete six-month follow-up visits for a total of seven visits (baseline and six follow-ups). During each follow-up visit (T1-T6), individuals will complete the cognitive and mini-physical performance assessments, biomarkers (e.g., blood pressure, BMI), and PROMIS measures targeting perceptions of social isolation, alcohol use, anxiety, depression, sleep problems, physical function, fatigue, ability to participate socially, and degree of pain interference with activities of daily living. The first participant was enrolled on January 20, 2024.

For the smartwatch sub-study, participants will wear an Apple Watch SE for 2 four-week periods, one during burn season and one during a non-burn period. Social isolation and cognitive function will be assessed during both the burn and non-burn seasons to identify potential changes in response to smoke-related air pollution (PM_2.5_). These outcomes are critical for understanding the health impacts of air pollution on cognitive and social well-being. Built and social environments (e.g., park spaces and ethnoracial composition) will be characterized at baseline and repeated if more current addresses or data become available during the study. Air quality monitoring will be continuous throughout the 36-month period. Table 1 shows the schedule of assessments and instrument collection by visit.

**Table 1 pone.0312660.t001:** Data collection schedule for 36-month study.

Data collected	T0^d^	T1 6 mo.	T2 12 mo.	T3 18 mo.	T4 24 mo.	T5 30 mo.	T6 36 mo.
ADRD assessment (MoCA v.8.1–8.3 and Cognigram)^a^		X	X	X	X	X	X
Sociodemographics^b^	X	X	X	X	X	X	X
Health conditions/behaviors^b^	X	X	X	X	X	X	X
Blood pressure, height, weight^a^		X	X	X	X	X	X
Mini Physical Performance Test (mini PPT)^a^		X		X		X	
Psychosocial measures (e.g., isolation)^b^		X	X	X	X	X	X
Anxiety, depression^b^		X	X	X	X	X	X
Sleep problems^b^		X	X	X	X	X	X
Physical function, fatigue, pain interference^b^		X	X	X	X	X	X
Ability to participate socially		X	X	X	X	X	X
Alcohol use^b^		X		X		X	
Air pollution monitors^c^	X	X	X	X	X	X	X

FU = Follow-up; mo = month; ^a^ From clinic assessment; ^b^ From questionnaire; ^c^ Monitors distributed at key sites within communities; ^d^ Screening visit

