All PurpleAir data from study-specific monitors are available for download through the PurpleAir Data Download Tool. Though there are not extensive publicly operating PurpleAir monitors in the study area, there are several PurpleAir monitors that operate east of the study area closer to the Atlantic coast, which in prior study campaigns (Sablan *et al*. 2024) [44] have been used to compare to data collected as part of our study. As of 2023, PurpleAir charges for data download for publicly operating monitors using a point-based billing system. Points range in value (100,000 to 1,000,000 per USD) depending on how many are purchased. The cost of data on a point basis depends on the data fields and number of observations requested. Based on prior work, the research team will leverage recently developed high-resolution fire-detection and Aerosol Optical Depth (AOD) products from NASA’s Moderate Resolution Imaging Radiospectrometer (MODIS), NOAA’s Visible Infrared Imaging Radiometer Suite (VIIRS), and the Geostationary Operational Environmental Satellite (GOES-16) to develop local climatologies of fire and smoke. This procedure leverages NOAA’s Hazard Mapping System (HMS) satellite-based observations to separate smoke from non-smoke influence. We will create daily kriged surfaces of bias-corrected PM_2.5_ for each study community for baseline and subsequent study years. Participants will be assigned exposures based on their home location. Based on daily estimates of PM_2.5_, we can aggregate the observations at any temporal resolution, including hour, day, week, month, and burn and non-burn seasons, to form the exposure assessment strategy for Aim 1.

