### Sample size/power

#### Sample size calculations for full sample

Sample size estimates were made to attain .8 power for Aims 1 and 2. The intraclass correlation was assumed to be .05 based on the cluster of neighborhoods within rural communities. For Aim 1a, an assumed effect size of *d* = .35 of the effect of PM_2.5_ on ADRD risk across burn seasons during the 3-year period was based on prior studies of cognitive decline and all-cause dementia in women related to PM_2.5_ [63]. Assuming 20 persons sampled per PM_2.5_ monitor area, this resulted in monitors covering 7 neighborhood block groups per community or N = 660 stratified across the 5 communities. For Aim 1b, effect size estimates for racial differences were based on findings of an approximately a twofold difference in hazard ratios of incident AD based on PM_2.5_ for non-Hispanic Black women compared to non-Hispanic White women or a difference in Cohen’s *d* = .45 [64] Assuming 20 persons sampled per PM_2.5_ monitor area, sample size estimates for power = .8 for the interaction of burn season by race, resulted in monitors covering at least 10 neighborhood block groups in each community for a total sample size of N = 1,000 stratified across the five communities. For Aim 2a, an assumed effect size of the built environment on cognitive function of *d* = .325 was based on Besser’s study finding of the relationship of proportion retail in 1/2-mile buffer to digit symbol coding as a measure of processing speed [65]. Assuming 20 persons sampled per neighborhood (census block), the sample size to detect an effect of the built environment on ADRD risk required six block groups per community for a total sample size of N = 600 stratified across five communities. Because Aim 1b provides the limiting sample size, the target sample size will be 1,000. Although there is a lack of literature to base the effect size for Aim 2b, the minimally detectable effect size with number of neighborhood block groups equal to 10 and n = 20 is *d* = .38. To account for 8% attrition [66–68], 1,087 participants will be recruited for the study. Conversions among risk measures and Cohen’s d were made in accordance with prior research and assumed a base rate = 0.107 of all-cause dementia [69]. Power analysis programs for mixed linear models, GLIMMPSE [70] CRT Shiny App [71] and PowerUp! [72] were used in these calculations.

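### The eligibility rule on extended absence names only the summer, so burn-season absence after the 12-month stay is neither excluded nor visibly recorded, although PM2.5 is assigned by home location

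*Protocol article*

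**What the plan says.** Four statements in the protocol article bear on this point.

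- **Screening and inclusion and exclusion criteria.** Residence is governed by two items: "Staying in the area for at least 12 months, and,Not leaving for an extended period during the summer months". No item names absence at any other time of year.
- **Setting.** Fields are burned "from ~October to May each year".
- **Specific aims, Aim 1a.** Social isolation and cognitive function are related to changes in PM2.5 "during agricultural burn and non-burn seasons over a 36-month period".
- **Air pollution data.** Daily PM2.5 surfaces are built for each study community, and "Participants will be assigned exposures based on their home location".

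The section on the T1–T6 sociodemographics and health survey lists the topics asked again at follow-up, among them contact details, living situation and employment. Time spent away from home is not among the topics listed.

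**The concern.** The exposure contrast in Aim 1 depends on where people are during the burn season. The one explicit absence rule applies to the season without burning. A person who spends part of a burn season elsewhere can be eligible, stays in the analysis, and is given the home-location PM2.5 for days when they were not there.

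This is error in the main exposure, in the window that carries the main contrast. If absence is unrelated to the outcomes, one would usually expect it to blur the difference between burn and non-burn seasons. If absence is related to health or to sensitivity to smoke, the error could be selective and its direction could not be predicted. The seasonal signal is also small: the Setting section gives increases of up to 2 μg/m³ over a low background.

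**Working it through.** **1. Which season the absence rule covers.** October to May is 8 calendar months, leaving June to September (4 months) as non-burn. The article does not define the summer months, but on any ordinary meaning they fall mainly or wholly in those four.

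**2. How much burn-season time the stay clause can cover.** The Timeline of study assessments fixes the follow-up: "Participants will return to complete six-month follow-up visits for a total of seven visits (baseline and six follow-ups", which runs to month 36.

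- Burn months per participant over follow-up: 3 years × 8 = 24.
- Burn months in any 12-month stay: 8.
- Burn months beyond the stay clause: 24 − 8 = 16, and 16/24 = 67%.

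This reads the stay clause generously, as barring long absences throughout its 12 months. If it means only that the person does not move away, it gives no protection against temporary absence even in year 1.

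**3. Size for one affected person.** Let k be the burn months spent away out of 8. The share of the assigned season average that comes from days not spent at home is k/8. The values of k are assumed, since the article gives none.

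| Months away (k) | Share of the assigned burn-season average |
|---|---|
| 1 | 1/8 = 12.5% |
| 2 | 2/8 = 25% |
| 3 | 3/8 = 37.5% |

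As an illustration, suppose the seasonal increase is the full 2 μg/m³, is even across the season, and is absent where the person stayed. At k = 3 the average increase actually met is 2 × 5/8 = 1.25 μg/m³, against 2 assigned, an overstatement of 0.75 μg/m³. With other air quality at the place of stay the error would differ and could reverse.

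**4. What cannot be computed.** The article gives no figure for how many participants would be away or for how long. The effect on the estimated PM2.5 coefficient therefore cannot be derived.

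**5. The attrition figure.** The sample size section states: "To account for 8% attrition [66–68], 1,087 participants will be recruited for the study". 1,000/(1 − 0.08) = 1,086.96, rounded up to 1,087, so the figure reproduces. Over three years, 8% corresponds to 1 − 0.92^(1/3) = 2.7% per year.

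**The case against.** The strongest reply is that a 12-month stay contains a whole burn season, so year 1 is covered, and that the summer rule has its own purpose in protecting the non-burn comparison. Both points have force: the rule is incomplete, not wrong. Nor can one argue that the summer clause would be redundant if the stay clause barred absence. The stay clause is limited to 12 months and the summer clause has no time limit, so they differ in scope. What stands is the gap after the stay period.

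Other safeguards help only in part.

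- Community research assistants contact participants every two months and might notice a long absence. The Discussion describes this contact as a retention measure and does not say that absences are recorded.
- Daily PM2.5 can be averaged over any window, and other integration windows are planned under Aim 1A. That makes a correction feasible, but only if dates away are known.
- The smartwatch data include location, but for about 120 participants and two four-week periods.
- The article summarises the survey, and the full instrument may ask about absence. If it does, only the use of that answer in the exposure average needs settling.

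That people bothered by smoke are the ones who leave is also unproven. The Setting section reports symptoms and less outdoor socialising during burns, not departure.

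A reader might infer more from the 12-month clause: that people planning to leave after T2 will push attrition above 8%, and that eligibility should require 36 months of intended residence. The document does not support this.

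- A loss of 5% to 10% per year after month 12 would give 1 − 0.95² = 9.8% to 1 − 0.90² = 19% by month 36, but those rates are assumed and appear nowhere in the text.
- Someone who leaves after T2 still gives two of the six outcome visits, and the planned mixed models can use them.
- Candidates must also be able to take part in study activities, so a site need not accept a declared leaver.
- A 36-month rule is a trade-off with representativeness. It could exclude mobile, disadvantaged residents whom the study sets out to reach.

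**Conclusion.** The point holds as a gap in the absence rule and in the handling of exposure. Extended absence in a burn season after the 12-month stay period is not excluded by any criterion, and the article describes no means of correcting for it, while PM2.5 follows the home location. About two thirds of each participant's burn-season months (16 of 24) lie outside the stay clause. For an affected person the misassigned share is k/8 of a season's average, or 12.5% to 37.5% for one to three months away.

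This rests on three assumptions: that burning fills October to May, that summer falls in the remaining months, and that the full survey does not already record absence. The number of people affected is unknown, so neither a bias in the PM2.5 effect nor a loss of power has been shown. The 8% allowance is reproduced and is not shown to be too low. This is a cheap improvement to exposure measurement, not a flaw that undermines the study.

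**What to change.** 1. **Remaining enrolment:** make the absence rule symmetric, for example: no extended absence planned in either the burn or the non-burn season. Leave the 12-month stay clause as it is.
2. **All participants, including those already enrolled:** at T1 to T6, record the dates of any extended absence from home since the last visit. If the full survey already asks this, no new item is needed.
3. **Analysis:** average daily PM2.5 over days in residence, or set the exposure window to missing when most of it was spent away. Do this at least as a sensitivity analysis beside the home-location average, and fix the definition of an extended absence beforehand.

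The cost is one question per visit, some extra exposure processing, and a few people no longer eligible. Enrolment began in January 2024, so those already in the cohort entered under the summer-only rule; the recorded dates allow both groups to be handled alike. Starting early matters, because dates of absence become harder to recover with each visit that passes.
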